### *Statistical Analysis Plan:*

A Phase II Safety, Tolerability, Pharmacokinetic and Pharmacodynamic Study of SFX-01 in Subarachnoid Haemorrhage, with exploratory efficacy evaluations. The study is a randomised, double-blind, parallel-group design comparing SFX-01 (300 mg) taken orally as capsules or as a suspension via a nasogastric tube (NG) twice-daily for up to 28 days versus placebo in 90 patients who have had SAH and present within 48 hours of ictus.

|                            |                                                                        |
|----------------------------|------------------------------------------------------------------------|
| Sponsor:                   | Evgen Pharma plc                                                       |
|                            | [name]
[name]
Liverpool
[name] |
| Author &
Qualifications | [name] M.Sc. C.Stat.                                             |

|                 |                  |
|-----------------|------------------|
| Document Date:  | 04 February 2019 |
| Version/Status: | Final            |

**DOCUMENT HISTORY**

| Version | Date        | Author       | Section/Page Amendment |
|---------|-------------|--------------|------------------------|
| Final   | 04 Feb 2019 | [name] | Finalised SAP          |

## List of Abbreviations and Definition Of Terms

|          |                                                        |
|----------|--------------------------------------------------------|
| AE       | Adverse Event                                          |
| ANOVA    | Analysis Of Variance                                   |
| ATC      | Anatomical Therapeutic Chemical                        |
| AUC      | Area Under the Curve                                   |
| bid      | Two times daily                                        |
| BICRO-39 | Brain Injury Community Rehabilitation Outcomes Scale   |
| BP       | Pain                                                   |
| CLCE-24  | Checklist for Cognitive and Emotional Consequences CRF |
| CRF      | Case Report Form                                       |
| CRP      | C-reactive protein                                     |
| CSF      | Cerebrospinal Fluid                                    |
| CSR      | Clinical Study Report                                  |
| CT       | Computed Tomography                                    |
| CV       | Coefficient of Variation                               |
| DCI      | Delayed Cerebral Ischaemia                             |
| DSA      | Digital Subtraction Angiography                        |
| DSMB     | Data Safety Monitoring Board                           |
| EOS      | End of Study                                           |
| EVD      | External Ventricular Drain                             |
| EW       | Emotional Well-Being                                   |
| GCS      | Glasgow Coma Scale                                     |
| GH       | General Health                                         |
| GOSE     | Glasgow Outcome Scale (Extended)                       |
| HL       | Hodges-Lehmann                                         |
| HP       | Haptoglobin                                            |
| ICH      | International Conference on Harmonisation              |
| ITT      | Intention-to-Treat                                     |
| IV       | Intravenous                                            |
| LP       | Lumbar Puncture                                        |
| MCA      | Middle Cerebral Artery                                 |
| MDA      | Malondialdehyde                                        |
| MedDRA   | Medical Dictionary for Regulatory Activities           |
| MFV      | Mean Flow Velocity                                     |
| MH       | Mental Health                                          |
| MMRM     | Mixed Model Repeated Measures                          |
| MRA      | Magnetic Resonance Angiography                         |
| MRI      | Magnetic Resonance Imaging                             |
| mRS      | Modified Rankin Scale                                  |
| NA       | Not Applicable                                         |
| NG       | NasoGastric                                            |
| PF       | Physical Functioning                                   |
| PK       | Pharmacokinetic                                        |
| PP       | Per-Protocol                                           |
| PTAE     | Pre-Treatment Adverse Event                            |
| RE       | Role Limitations Due to Emotional Problems             |
| RP       | Role Limitations Due to Physical Health                |
| SAE      | Serious Adverse Event                                  |
| SAH      | Subarachnoid Haemorrhage                               |
| SAP      | Statistical Analysis Plan                              |
| SAHOT    | Subarachnoid Haemorrhage Outcome Tool                  |

EVG001SAH Statistical Analysis Plan

SF  
SF-36  
SFN  
SFX-01

SOC  
TCD  
TCTC  
TEAE  
VT  
WBC  
WFNS  
WHODD  
Z

Social Functioning  
Short Form (36) Health Survey  
Sulforaphane  
The Investigational Medicinal  
Product/stabilised Sulforaphane  
System Organ Class  
Trans-Cranial Doppler  
The Clinical Trial Company Ltd  
Treatment Emergent Adverse Event  
Energy/Fatigue  
White blood cells  
World Federation of Neurosurgical Scale  
World Health Organization Drug Dictionary  
Standardized Normal Distribution Test  
Statistic

## 1 Introduction

This document describes the objectives, analysis populations, endpoint derivations, statistical analyses and data presentations to be performed for the clinical protocol EVG001SAH entitled “SFX-01 After Subarachnoid Haemorrhage (SAS Study)”. This is the final version of the SAP text, approved in February 2019 which updates previous draft versions of the SAP to provide more detail on endpoint derivations and the analyses to be performed. In general, details of the study design that can also be found in the protocol have been removed from this version. The supporting tables, listing and figures will be finalised in a separate document. Any changes made in the course of the evaluation and analysis of these data performed after the locking and un-blinding the database will be documented and fully justified in the final Clinical Study Report (CSR). The contents of the SAP are consistent with the principles described in the ICH E8 and E9 guidelines .

## 2 Objectives

### Primary:

To evaluate the safety of up to 28 days of SFX-01 dosed at up to 92 mg Sulforaphane (SFN) per day.

To investigate the pharmacokinetic properties of SFN in cerebrospinal fluid (CSF).

To determine if a minimum of 7 days treatment with SFX-01 reduces Middle Cerebral Artery (MCA) peak flow velocity following Subarachnoid Haemorrhage (SAH).

### Secondary:

To determine if a minimum of 7 days treatment with SFX-01 improves clinical outcome following SAH as measured using the modified Rankin Scale assessed at 7 days, discharge, 28, 90 and 180 days post ictus.

To determine blood SFN levels (and its metabolites) with treatment with SFX-01 (300mg bid).

To determine CSF SFN levels and kinetics with treatment with SFX-01 (300mg bid).

To determine if up to 28 days treatment with SFX-01 increases blood haptoglobin (HP) levels and decreases malondialdehyde (MDA) levels following SAH.

To determine if up to 28 days treatment with SFX-01 can reduce the incidence of Delayed Cerebral Ischaemia (DCI) following SAH.

To determine if up to 28 days treatment with SFX-01 improves long-term outcome in subjects following SAH.

To determine if up to 28 days of treatment with SFX-01 can reduce iron deposition and cortical atrophy following SAH.

### 3 Study Design

The study is a randomised, double-blind, parallel-group design comparing SFX-01 (300 mg bd) administered for up to 28 days versus Placebo control in 90 patients who meet the per-protocol criteria for efficacy analyses, who have had a SAH and are referred to neurosurgical units for tertiary care.

Treatment is taken twice-daily either orally or via nasogastric tube (NG). For the first 20 patients, treatment duration is determined by the length of time spent in tertiary care (up to Day 28 post ictus). Following a DSMB review (as per protocol) for all subsequent patients the intended treatment duration is 28 days regardless of whether they remain in tertiary care for the full 28-day period. After treatment all patients are then followed up at discharge from the neurosurgical unit and then subsequently on Day 28, Day 90 and Day 180 post ictus.

A separate and more detailed investigation (sub-study) of the pharmacokinetic properties of SFN parent drug, and the primary metabolite, both in CSF and blood is also undertaken. This will involve up to 12 patients who have an External Ventricular Drain (EVD) fitted as part of their normal standard of care and is undertaken on two separate occasions within the first 7 days post ictus.

The protocol was amended part way through recruitment to stratify the randomisation by WFNS score (1-3 v 4-5) and centre.

#### 3.1 Sample Size

Following protocol amendment 5, the sample size was increased from 90 to up to 120 patients in order to provide 90 who would meet the per protocol criteria and be evaluable for the primary efficacy analysis. Furthermore, this protocol amendment also specified that patients who had potentially received insufficient or incorrect study medication may be replaced.

If the standard deviation is approximately half (53%) of the mean difference in the maximum MCA flow velocity, 90 evaluable patients will have 80% power to detect a statistically significant difference between treatment arms using a 1-sided type 1 error rate of 5%. Statistical significance will be declared if the 2-sided p-value is  $<0.05$ , in this case the trial will have  $>80\%$  power with 90 evaluable patients if the standard deviation is  $<59\%$  of the mean difference.

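### The SAP's power statement (section 3.1) inverts its ratio: 80% power with 90 patients holds when the mean difference is about 53% or 59–60% of the SD, not the reverse

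*SAP*

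**What the plan says.** SAP section 3.1 gives two power conditions, each expressing the SD as a percentage of the treatment difference.

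- First: "If the standard deviation is approximately half (53%) of the mean difference in the maximum MCA flow velocity", then "90 evaluable patients will have 80% power to detect a statistically significant difference between treatment arms", "using a 1-sided type 1 error rate of 5"%.
- Second, for the test that will actually be used: "Statistical significance will be declared if the 2-sided p-value is" below 0.05, in which case the trial is said to have more than 80% "power with 90 evaluable patients if the standard deviation is" less than 59% of the mean difference.

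The same section explains that "the sample size was increased from 90 to up to 120 patients in order to provide 90 who would meet the per protocol criteria". The 120 is therefore an allowance for non-evaluable patients, and 90 is the number that enters the power calculation. The SAP gives no absolute SD, absolute difference or allocation ratio. No other section restates or corrects the two conditions.

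**The concern.** An SD of about half the difference means an effect of nearly two SDs. A two-arm comparison of 90 patients is not needed to find an effect of that size with 80% power, so the sample size and the stated condition do not fit together.

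The two sentences also do not fit each other. With the number of patients and the power held fixed, a stricter test needs a larger effect relative to the SD, so the SD that can be tolerated, as a share of the difference, must fall. In the SAP it rises, from 53% (1-sided) to 59% (2-sided).

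At stake is the only power justification that the SAP gives for the primary endpoint. A reader who takes it at face value would think the trial sensitive only to effects of 1.7 to 1.9 SD, and would read a non-significant result as excluding only very large effects.

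**Working it through.** **Inputs.** From SAP section 3.1: 90 evaluable patients; 80% power; 5% 1-sided with 53%; 5% 2-sided with 59%. From SAP section 3: two parallel arms. Assumed: 1:1 allocation, so n = 45 per arm. Let d = mean difference / SD. Because d is a ratio, no absolute velocity is needed.

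**Step 1: what 45 per arm can detect with 80% power.** Normal approximation: d = (z for alpha + z for power) × √(2/n), with √(2/45) = 0.2108.

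- 1-sided 5%: (1.645 + 0.842) × 0.2108 = 0.524. Noncentral t: 0.528.
- 2-sided 5%: (1.960 + 0.842) × 0.2108 = 0.591. Noncentral t: 0.597.

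These are the SAP's 53% and 59%, but as difference divided by SD.

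**Step 2: power if the SAP's percentages are read as difference / SD.** Normal approximation: power = Φ(d × √(n/2) − z for alpha), with √(45/2) = 4.743.

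- d = 0.53, 1-sided: Φ(2.514 − 1.645) = 80.8%. Noncentral t: 80.2%.
- d = 0.59, 2-sided: Φ(2.799 − 1.960) = 79.9%. Noncentral t: 79.0%. At d = 0.60 the noncentral t gives 80.4%.

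Both stated power figures are recovered to rounding.

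**Step 3: power if the sentences are read as printed.**

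| Condition as printed | d | Power, 45 per arm | Smallest n per arm for 80% (noncentral t) |
|---|---|---|---|
| SD = 53% of difference, 1-sided | 1/0.53 = 1.89 | above 99.99% | 5 (85.8%; 4 gives 76.1%) |
| SD = 59% of difference, 2-sided | 1/0.59 = 1.69 | above 99.99% | 7 (82.9%; 6 gives 75.4%) |

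Taking 90 as the number per arm only pushes the literal power higher.

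**Step 4: the allocation assumption.** Under 2:1 allocation the inverted ratios give 76.6% (1-sided) and 75.1% (2-sided) by the normal approximation, a worse fit. The 1:1 ratio reproduces both figures.

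**Step 5: a check that does not depend on allocation.** For fixed patient numbers and power, moving from the 1-sided to the 2-sided test multiplies the detectable d by (1.960 + 0.842)/(1.645 + 0.842) = 1.13. The SAP's figures move by 0.59/0.53 = 1.11, which fits difference / SD. If 53% were truly an SD / difference threshold for the 1-sided test, the 2-sided threshold would be 0.53/1.13 = 0.47, not 0.59.

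**Step 6: size of the misstatement.** Stated effect over actual detectable effect: 1.89/0.53 = 3.6 (1-sided) and 1.69/0.597 = 2.8 (2-sided), so about threefold. Put the other way round, the SD may be up to about 1/0.53 = 189% of the difference (1-sided) or about 1/0.59 = 169% (2-sided).

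**The case against.** The strongest reply is that this is a transposition in descriptive text. The calculation behind it is evidently sound, 90 evaluable patients is consistent with it, and no p-value, estimate or population depends on the sentence. All of that stands, and it limits the matter to wording. It does not rescue the statement, which misdescribes what the trial can detect.

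The second sentence is also not strictly false: power does exceed 80% whenever the SD is below 59% of the difference. That stands too. The fault there is that 59% is presented as the threshold and is not one. Only the first sentence is numerically wrong as printed.

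A reader might take 0.59 against 0.60 as a further error. The documents do not support that. The normal approximation gives 0.591 and the noncentral t gives 0.597, so 59% is a rounded value from an ordinary method. The planned primary model (SAP section 6.4) is covariate-adjusted on the log scale, so neither two-sample formula is exact for it.

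Finally, 1:1 allocation is an assumption here. The fit to both percentages makes it very plausible, and the inconsistency between the two sentences (step 5) does not need it.

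**Conclusion.** Wrong as written. Section 3.1 states the reciprocal of the intended ratio in both sentences. Assuming 45 per arm, 90 evaluable patients give 80% power at a mean difference of about 53% of the SD (1-sided 5%) or about 59–60% of the SD (2-sided 5%). The printed text implies 1.89 and 1.69 SD, an overstatement of the smallest detectable effect of about threefold.

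Two stronger readings are tempting, and neither holds.

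- A reader might infer that the trial is underpowered or that 90 is the wrong number. It is not shown to be: 90 fits the inverted ratios.
- A reader might infer that the error flatters the trial, so that a null result would be taken to rule out smaller effects than it can. The direction is the opposite. The printed text understates the trial's sensitivity, and correcting it makes the stated property more favourable.

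**What to change.** Replace the two power sentences in SAP section 3.1, turning round both the ratio and the inequality. For example:

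*Assuming 1:1 allocation, 90 evaluable patients give 80% power at a 1-sided 5% level if the mean difference in maximum MCA flow velocity is at least about 53% of the SD. At the 2-sided 5% level used to declare significance, power is at least 80% if the mean difference is at least about 60% of the SD.*

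The sponsor should confirm the allocation ratio when making the change. The figure of 60% is the noncentral t value rounded; about 59% is acceptable if the text says that it comes from the normal approximation. Carry the corrected wording to the clinical study report.

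The cost is two sentences. Enrolment, the significance level and the analysis model do not change.

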## 4 Analysis Populations

Data from this study will be analysed on two occasions although efficacy endpoints will only be analysed on one occasion. The data cut-off for the first analysis of the study will be 28 days after the last patient is randomized. After this first data-cut-off, the TCD data will be analysed and available safety and PK data will be reported. The second data cut-off will occur 6 months after the last patient is randomized. This second and final analysis will include all available safety, pharmacokinetic and secondary efficacy endpoint data.

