#### **5.15 Time-Windows**

The protocolled defined visit windows for assessments are +/-1 for Day 7, -2 at Discharge, -6/+2 at Day 28, +/-14 at Day 90 and +/-28 at Day 180. However, for the purpose of any timepoint analyses, data will be included at the visit closest to the time the recordings were taken.

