## **6.7 Missing Data Diagnostics**

For the mRS, GOSE, SAHOT, CLCE, BICRO and SF-36 endpoints, if more than 15% of patients have missing data for the respective endpoint in either treatment arm at Day 180, the possible impact of these data on the primary analyses will be explored as follows:

- For all endpoints the number of patients with missing data will be summarised. In addition, baseline WFNS score (1-3 v 4-5) will be summarized by treatment arm for each endpoint at each timepoint according to whether data were missing at that timepoint.
- For mRS and GOSE only the analysis at each timepoint will be repeated by carrying forward the outcome from the most recent timepoint with recorded data.

The purpose of these analyses is to assess whether the amount of missing data differs by treatment arm and whether patients with missing data initially had a worse prognosis or were performing worse on other measures recorded at the same timepoint. For example, if there

are more patients in the placebo arm with missing data and those that have missing data were tending to respond less well, this would suggest the treatment effect may have been underestimated.

If the results are marginal for a particular endpoint these investigations may be performed despite neither arm having 15% of patients with missing data. Dependent on results further analyses may be performed to assess the possible impact of missing data.

For TCD endpoints it is not anticipated that missing data could have a bearing on the outcome of the results given the proximity of the measurements to dosing.

Only the year of birth has been recorded. When calculating age, a date of birth of 1st July will be assumed.

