## **6.8 Subgroup analyses**

Subgroup analyses will be performed for maximum post-dose MCA mean flow velocity, mRS at 90 days and GOSE at 90 days for the following variables: centre, WFNS score (1-3 v 4-5), Fisher grade, time from ictus (<24h, 24-48h, >48h), Age group ( $\leq 49$ , 50-59,  $\geq 60$ ), gender, surgical procedure (coiling, clipping, not done), location of aneurysm (anterior, posterior), main vessel of aneurysm (anterior, middle, internal, vertebrobasilar) and whether the patient developed a secondary bleed prior to randomisation. Additionally, a subgroup analysis of the primary TCD endpoint will be performed by baseline value split according to quartiles. Results will not be presented for any subgroup level that contains fewer than 10 patients.

Data will be analysed separately for each level of the subgroup. For the primary TCD endpoint, the ANOVA model will be re-run and the treatment effect and associated 95% confidence intervals presented. For mRS and GOSE at 90 days, the logistic regression model will be performed within each level of the subgroup with the odds ratio and associated 95% confidence intervals presented. Results from all subgroups will be presented in a forest plot for each endpoint separately.

If there is evidence of heterogeneity of the treatment effect amongst subgroups the following tests will be performed:

1. A treatment-by-subgroup interaction term will be added to a model containing the terms included in the primary analysis model together with the main effect of the subgroup if not already included in the model. The p-value for the change in model fit by adding the interaction term will be presented
2. A test of the collective heterogeneity amongst subgroups will be performed. This will be achieved by comparing a base model including treatment and all main effects of subgroups with a model containing all two-way interactions of treatment and subgroup. The p-value for the change in model fit by adding all of the interaction terms simultaneously will be presented and described as a global interaction test.

Age will be fitted as a continuous covariate in the interaction tests.

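### The final data cut-off falls about 3-4 weeks before the Day 180 visit window closes for the last patient, so late but in-window Day 180 assessments can be lost

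*SAP*

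**What the plan says.** Section 4 of the SAP provides for two data cut-offs. On the second it states: "The second data cut-off will occur 6 months after the last patient is randomized". It goes on: "This second and final analysis will include all available safety, pharmacokinetic and secondary efficacy endpoint data". No further cut is described. Section 6.3 relies on each endpoint being analysed only once.

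The visits run on a different clock. Section 3 schedules follow-up at discharge and "subsequently on Day 28, Day 90 and Day 180 post ictus". Section 5.15 lists the permitted windows, ending with +/-"14 at Day 90 and +/-28 at Day 180". It then adds that "for the purpose of any timepoint analyses, data will be included at the visit closest to the time the recordings were taken".

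On the delay between ictus and randomisation, the title page describes "patients who have had SAH and present within 48 hours of ictus", while Section 6.8 has a subgroup for "time from ictus (<24h, 24-48h, >48h"). The exact lag is not stated.

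**The concern.** One rule counts six months from the last randomisation. The other counts 180 days from each patient's ictus and tolerates 28 days either way. The cut-off comes shortly after the nominal Day 180 visit of the last patient, so it leaves almost none of the late half of the window. A visit held in that late half meets the window in Section 5.15 but takes place after the date that closes the final analysis.

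At stake are the six instruments formally analysed at Day 180 (Table 11): mRS, GOSE, SF-36, SAHOT, CLCE-24 and BICRO-39. Long-term outcome is a secondary objective, and Day 180 mRS is named in another. A visit lost this way also counts as missing under Section 6.7, where diagnostics start "if more than 15% of patients have missing data for the respective endpoint in either treatment arm at Day 180". For mRS and GOSE, the conditional carry-forward analysis could then use an earlier score in place of an assessment that was actually made within its window.

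**Working it through.** The SAP gives no figure of its own for this gap, so there is none to reproduce. The check is calendar arithmetic.

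**Inputs from the SAP**
- Cut-off: last randomisation + 6 months (Section 4).
- Day 180 window: 180 ± 28 days post ictus (Sections 3 and 5.15).
- Sample size: 90 evaluable, up to 120 randomised (Section 3.1).

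**Assumptions**
- Lag from ictus to randomisation: 0-2 days, based on presentation within 48 hours. Lags of 3-4 days are also tried because Section 6.8 has a level beyond 48 hours.
- Accrual: 1-6 patients per month. The SAP gives no rate.

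**Step 1: length of the window.** It opens on Day 180 − 28 = 152 and closes on Day 180 + 28 = 208. That is 208 − 152 + 1 = 57 days.

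**Step 2: cut-off on the last patient's own clock.** Over all start dates in 2018-2020, six calendar months is 181-184 days. Cut-off day = lag + 181 to 184, and gap = 208 − cut-off day.

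| Ictus counted as | Lag (days) | Cut-off, day post ictus | Gap to Day 208 (days) |
|---|---|---|---|
| Day 0 | 0 | 181-184 | 24-27 |
| Day 0 | 1 | 182-185 | 23-26 |
| Day 0 | 2 | 183-186 | 22-25 |
| Day 0 | 3-4 | 184-188 | 20-24 |
| Day 1 | 0-2 | 182-187 | 21-26 |
| Day 1 | 3-4 | 185-189 | 19-23 |

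For lags of 0-2 days with ictus as Day 0, the gap is 22-27 days, or 3.1-3.9 weeks. As a share of the window this is 22/57 = 39% to 27/57 = 47%. No combination tried brings the gap below 19 days.

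**Step 3: what is kept.** The nominal Day 180 visit falls 181 − 180 = 1 to 186 − 180 = 6 days before the cut-off. A last patient seen on or before Day 180 is retained.

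**Step 4: who is exposed.** A patient randomised d days before the last one has d more days before the cut-off. The window is truncated only while d is less than the gap, so this concerns the last 22-27 days of recruitment. Exposed patients = monthly rate × gap / 30.4:
- 1 per month: 22/30.4 = 0.7 to 27/30.4 = 0.9
- 3 per month: 2.2 to 2.7
- 6 per month: 4.3 to 5.3

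**Step 5: expected loss.** Suppose visits are spread evenly over the 57 days. Averaged over exposed patients, the chance of a visit after the cut-off is (gap + 1)/(2 × 57), which is 23/114 = 0.20 to 28/114 = 0.25. Expected losses are then:
- 1 per month: 0.7 × 0.20 = 0.1 to 0.9 × 0.25 = 0.2 patients
- 3 per month: 2.2 × 0.20 = 0.4 to 2.7 × 0.25 = 0.7 patients
- 6 per month: 4.3 × 0.20 = 0.9 to 5.3 × 0.25 = 1.3 patients

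If every exposed patient attended at the very end of the window, all of the roughly 1-5 would be lost.

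**Step 6: effect on the missing-data trigger.** With 90-120 patients split evenly (assumed), an arm holds 45-60. One lost patient adds 1/60 = 1.7 to 1/45 = 2.2 percentage points against the 15% threshold.

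**The case against.** The strongest reply is that the plan does cover the scheduled visit. Even for the last patient the nominal Day 180 precedes the cut-off, and exposure is not loss. This stands. A reader might infer that valid assessments will be cut off as a matter of course, but the SAP supports only that they can be, and only in late recruits who attend late.

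It can also be said that six months is a loose label for the Day 180 follow-up and that all available data are promised. Section 5.11 does censor length of stay at the cut-off, but that is routine administrative censoring, and Section 7 censors survival at the End of Study visit instead. The SAP nowhere says expressly that a visit just after six months would be discarded. This stands in part. Equally, nothing in the SAP lets such a visit in, and the analysis is called final.

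Third, Day 208 is not the limit for analysis, because Section 5.15 assigns data to the nearest visit, so any fixed date truncates something. That is correct, but it does not remove the mismatch: under the nearest-visit rule, the cut-off is the only thing that would exclude a late in-window assessment.

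Finally, the endpoints that carry the trial are out of reach. The primary endpoint is maximum MCA flow velocity, the two key secondary endpoints are mRS and GOSE at 90 days (Section 6.3), and the Section 6.8 subgroup analyses use only these. The carry-forward analysis is a conditional sensitivity analysis. All of this stands and limits the weight of the point.

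**Conclusion.** Sections 4 and 5.15 do not fit together. For the last patient, the final cut-off falls 22-27 days before the Day 180 window closes, assuming 0-2 days from ictus to randomisation. The gap is still at least 19 days under the other lags and day-counting conventions tried. The result is a truncated window for patients randomised in roughly the last 3-4 weeks of recruitment.

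The consequence is small. About 1-5 patients are exposed at an assumed 1-6 per month, and probably about one or fewer is lost if visits are spread evenly over the window. Only Day 180 secondary analyses are touched. One patient moves an arm's missing-data rate by about 2 percentage points, so this alone is unlikely to set off the 15% trigger.

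A reader might also infer a bias between arms. The SAP does not support that: the truncation follows calendar time in a randomised, double-blind trial, and nothing in it points towards one arm. This is a minor inconsistency that is cheap to remove.

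**What to change.** In Section 4, define the second data cut-off as the first date on which every randomised patient has completed the Day 180 visit, died, withdrawn, or passed Day 208 post ictus.

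The condition should apply to every patient. If the date were tied only to the last-randomised patient's visit and that patient attended early, someone randomised a few days before could still be cut off.

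The cost is one sentence of SAP text, with no new data or analysis. At most, the cut-off moves to Day 208 of the latest patient. At a lag of 0-2 days that is about 206-208 days after the last randomisation, or 22-27 days later than now, so database lock may slip by up to about 4 weeks. If the late recruits are seen on time, there is no delay.
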